### Study population

Patients and relatives can participate together in the study, in the same or separate groups, as preferred. Patients can also participate without a relative and vice versa. Relatives can be partners, parents, children and other significant others such as close friends or neighbors.

Inclusion and exclusion criteria are described in Table 2 for patients and Table 3 for relatives.

**Table 2 Tab2:** patients’ inclusion and exclusion criteria

Inclusion criteria	Exclusion criteria
Having advanced cancer (defined as having no curatively aimed treatment options available, only life-prolonging or palliative treatments)	Younger than 18 years of age
Conform WHO performance status of 0 or 1 (34)	Unable to provide written informed consent
Able to read and speak the Dutch language	Not willing to use a camera
Access to a computer or laptop and internet

**Table 3 Tab3:** relatives’ inclusion and exclusion criteria

Inclusion criteria	Exclusion criteria
Relative of a patient with advanced cancer	Younger than 18 years of age
Able to read and speak the Dutch language	Unable to provide written informed consent
Access to a computer or laptop and internet	Not willing to use a camera

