### Statistical analysis

We will follow the intention-to-treat principle for the analyses of the primary and secondary outcomes. Descriptive statistics will be used to summarize patient characteristics (age, gender, ethnicity, Social Economic Status, marital status, cancer type and time since diagnosis).

For the patient outcomes, we will use linear mixed models with a random intercept to adjust for repeated measures over time. As fixed effects, we will include time points of measurement (baseline, 8 weeks and 16 weeks) and a variable denoting when the participant received the program at each time point (early versus late starters). To adjust for possible confounding, we additionally will add age, sex, ethnicity, Social Economic Status, cancer type and time since diagnosis as fixed effects to the model.

Furthermore, we will assess whether there is a dose-response relationship between the number of sessions of the program and outcome. We will perform a similar analysis as for the main effect, but include the number of sessions instead of the intervention group.

The quantitative data analyses for relatives will be conducted in a similar way but it will have an explorative nature due to its expected lower number of participants.

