Our SMART study has several risks. The study population and the program contain several factors that cannot be fully controlled. Firstly, there will be a considerable risk of drop out, either partly (some meetings) or completely, to disease progression or treatment burden of our vulnerable population [59]. To minimize this, we only include patients with a WHO performance status of 0 or 1 [60], and participants can choose when to start with the program to accommodate their schedule. Secondly, the risk of selection bias cannot be ruled out. Conducting research through self-referral, by online questionnaires and the video-conferencing group format, may primarily attract participants with higher digital literacy [61]. To minimize this risk, we offer technical support before and during the program, and explicitly explain that experience with video-conferencing applications is not necessary. Banbury and colleagues demonstrate that inexperience with video-conferencing or computer use was not a major problem for participation in video-conferencing groups [22]. Thirdly, while a randomized controlled trial (RCT) is preferred as a gold standard for measuring the effects of an intervention, we opt for a non-randomized stepped wedge design to make the study better feasible. Whilst we adjust for possible confounders in the analysis, residual confounding still remains a risk. Fourth, our program is a complex intervention, meaning it contains several interacting components, such as improving self-efficacy and behavior, the self-tailoring format, and group interaction [62]. Therefore, it may be difficult to identify the active components of the program. Combining the quantitative data of this study with the findings of our complementary qualitative study will provide insight into participants’ experiences and the perceived working mechanism of the program.

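### The planned session-count analysis can show a beneficial slope when the program has no effect, because worsening health is an expected reason for missing meetings and the model does not account for it

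*Protocol article*

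**What the plan says.** The protocol article, Statistical analysis, announces that "we will assess whether there is a dose-response relationship between the number of sessions of the program and outcome" and specifies it in one sentence: "We will perform a similar analysis as for the main effect, but include the number of sessions instead of the intervention group". The main-effect model is described just before: "we will use linear mixed models with a random intercept to adjust for repeated measures over time", with measurement time points and the early/late program variable as fixed effects. To deal with confounding, the authors will "add age, sex, ethnicity, Social Economic Status, cancer type and time since diagnosis as fixed effects to the model".

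The Discussion, listing the study's risks, says that "there will be a considerable risk of drop out, either partly (some meetings) or completely, to disease progression or treatment burden of our vulnerable population". In answer, it points to the entry criterion ("Conform WHO performance status of 0 or 1") and to the free choice of start date. It also concedes that residual confounding may remain, but makes that remark about choosing a non-randomized design, not about the session count. The relatives' analyses are labelled explorative. The patients' dose-response analysis carries no such label.

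**The concern.** For someone in the program, the number of sessions is not assigned. It depends in part on how the patient fares after baseline, and the protocol names worsening illness and treatment burden as reasons for a low count. If the same decline also lowers constructive attitudes, quality of life or self-efficacy, or raises fatigue, pain or HADS scores, then low attendance and poor outcome share a cause that the model leaves out.

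The listed covariates are fixed patient characteristics. The random intercept absorbs stable differences between persons, not deterioration during the study. Performance status is only an entry criterion. A positive slope could therefore appear without any benefit from the sessions. At stake is how that slope is read: in a non-randomized study, a dose-response gradient is easily taken as corroboration of the main result.

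**Working it through.** **The plan's own figure.** Sample size calculation: 104 evaluable patients and 20% drop-out give 104 / (1 − 0.20) = 130, as stated. Nothing below changes this figure.

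**Inputs from the protocol.** Six sessions; measurements at baseline, 8 and 16 weeks; early starters exposed at weeks 8 and 16, late starters at week 16 only; 104 patients; individual autocorrelation 0.7; significance 0.05 (sidedness not stated, two-sided assumed); design effect 0.5 SD. "Number of sessions" is read as sessions attended.

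**Inputs that had to be assumed.** The documents give no attendance distribution, no rate of decline and no effect of decline on the outcome. Two sets of assumptions were simulated, 2000 trials per scenario in set B, all with a true program effect of zero and with sessions replacing the program variable as the protocol states.

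*Set A, graded decline.* Half the patients start early; mean attendance is about 5.1 of 6; decline correlates about 0.5 with the tendency to miss sessions. One-sided test, nominal 2.5%; two implementations.
- 1 SD of decline lowers the outcome by 0.2 SD: false positives 7 to 8%, spurious effect about 0.07 SD over six sessions.
- 1 SD of decline lowers it by 0.4 SD: false positives 13 to 15%, spurious effect about 0.12 SD.

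*Set B, some patients decline.* Attendance per session falls from 95% to 35% once a patient declines. Two-sided test, nominal 5%.

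| Patients declining | Outcome drop | Decliners' follow-up missing | Spurious effect, six sessions | Rejection |
|---|---|---|---|---|
| 30% | 0.5 SD | none | 0.11 SD | 12.9% |
| 30% | 0.5 SD | half | 0.08 SD | 10.4% |
| 30% | 0.8 SD | none | 0.18 SD | 26.4% |
| 40% | 0.5 SD | none | 0.13 SD | 16.1% |
| 40% | 0.8 SD | none | 0.20 SD | 30.4% |
| 30% | none | none | 0.00 SD | 5.6% |
| 30%, attendance unaffected | 0.5 SD | none | 0.00 SD | 5.4% |

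In the five biased rows nearly all rejections favour the program. The Monte Carlo standard error near 5% is √(0.05 × 0.95 / 2000) = 0.5 percentage points, so the last two rows are consistent with nominal. Both links, decline to attendance and decline to outcome, are needed for the bias.

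**How strong is the assumed attendance link?** Without it, mean attendance is 6 × 0.95 = 5.70. With it, the simulated mean is 5.16 at 30% declining and 4.98 at 40%. Per decliner, that is (5.70 − 5.16) / 0.30 = 1.8 and (5.70 − 4.98) / 0.40 = 1.8 sessions lost on average.

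**Same data, main model.** With the program indicator in place of the session count, the estimate is about 0.00 SD and rejection 5 to 6%. The problem belongs to the session-count analysis alone.

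**Scale.** Relative to the 0.5 SD design effect, 0.11 / 0.5 = 22% and 0.20 / 0.5 = 40%; the mildest set A case is 0.07 / 0.5 = 14%.

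**A possible check within the trial.** Late starters begin after 8 to 10 weeks, so their change from baseline to week 8 cannot be caused by sessions attended later. In simulation, the mean slope of that change on later attendance is 0.00 per session with no health effect, 0.05 when 1 SD of decline costs 0.2 SD, and 0.09 at 0.4 SD. With about 52 late starters, however, the slope is significant in only about 8% of trials at 0.2 SD and 15 to 18% at 0.4 SD, against about 3% with no selection.

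**The case against.** The strongest reply is that this is one supplementary analysis, absent from the abstract and the objectives, and that caveats and sensitivity checks for it may sit in a full protocol or analysis plan not shown here. That limits the weight of the point but does not answer it: the article itself fixes the exposure, the substitution and the covariates carried over.

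A second reply is that the bias is modest and every size rests on assumptions. This stands. Zero-session control observations contribute to the slope and dilute the bias, and under the mildest inputs false positives only rise from 2.5% to about 7%. The effect of decline on the primary outcome is plausible but not stated. The Discussion describes a risk, not an observed pattern.

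Some stronger readings are tempting, and the documents do not support them.
- A reader might infer that health decline by itself must produce a gradient. It can do so only if it also lowers the outcome.
- A reader might simulate the gradient among exposed patients, with both exposure and sessions in the model, and find false-positive rates of 19% to 51%. The protocol does not plan that model; it will "include the number of sessions instead of the intervention group".
- A reader might infer that the authors intend to claim causality from the slope. The article says only that they will assess the relationship.

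**Conclusion.** The concern holds as a matter of specification and interpretation. The article makes a post-baseline count the exposure, expects that count to fall "either partly (some meetings) or completely, to disease progression or treatment burden of our vulnerable population", and includes nothing in the model to separate the two. If decline also lowers the outcomes, the model as written can show benefit where there is none: roughly 0.1 to 0.2 SD over six sessions, with false positives of about 7 to 15% (one-sided 2.5%) or 10 to 30% (two-sided 5%) over the ranges tried. The direction was stable across those ranges; the size depends on the assumed rate of decline, its effect on attendance and its effect on the outcome. If the session count meant meetings scheduled rather than attended, this point would not arise.

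A reader might extend the criticism to the main result. That is not supported: the primary intention-to-treat model does not use attendance, and neither it nor the sample size is touched by this point. It is a cheap improvement to a secondary analysis, worth making because it changes what a positive slope may be said to show.

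**What to change.** 1. In Statistical analysis, define this as an exploratory association between attendance and outcome, not as a dose effect or as support for causality.
2. Add baseline fatigue, pain and HADS, already in the patient questionnaire, as covariates, and state that this does not remove decline that starts after baseline. Adjusting for the same scores at weeks 8 and 16 is not a simple remedy, because they are also outcomes that the program may change.
3. Have the study team record the reason for each missed meeting (illness or treatment versus other). The logbook is not suited to this: it is completed after a meeting, and a participant who missed it may not fill it in. As a sensitivity analysis, repeat the model counting only absences not due to illness or treatment as lost sessions. If these are rare (6 × 0.05 = 0.3 per patient under the set B assumption), that slope will largely restate the program contrast and say little about dose. The simulations did not test this step.
4. Optionally, report the late starters' baseline-to-week-8 change against later attendance as a supporting check. A non-zero slope signals selection. A null slope must not be read as reassurance, given power of about 8 to 18%, and the check misses decline that begins after week 8.

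Cost: a few lines of text, one attendance item kept by the team, and a weaker claim. No extra patients or visits are needed.

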### Qualitative research

A complementary qualitative study will be carried out to explore the lived experiences of participants with the “Living with Cancer” program. Data concern the recordings of the video-conferencing groups and participants’ logbooks. We will conduct inductive, thematic content analyses [54, 55] describing their experiences with the program, including their perceived value of group-based peer support, the video-conferencing format, and the approach of including both persons with advanced cancer and relatives. We will also explore the perceived working mechanism of the program.

## Discussion

Self-management for persons with advanced cancer and their relatives is multifaceted due to multilayered consequences and the uncertainties they face. To our knowledge, there is a lack of research into peer self-management support for this population.

The SMART study aims to fill this gap in knowledge. We will evaluate a self-management program to support persons with advanced cancer and their relatives. The program has been built on the CDSMP, an evidenced-based peer self-management support program for persons with chronic conditions [12, 13]. New features are its use for persons with advanced cancer, the inclusion of relatives, and the video-conferencing format for this population. The use of both quantitative and qualitative analyses will provide valuable insight into the effectiveness and value of this program.

Peer support for persons with advanced cancer and their relatives has rarely been researched [17]. Although the concept of peer support dates back several centuries, it is only in the last few decades that it has tracked attention in healthcare. In the field of mental health, there is an international growing trend to adopt peer support [56]. The literature suggests that peer support is beneficial in mental health care, such as improved health-related quality of life and improved patient activation [56]. In this study, we will now explore its value, as part of a self-management support program for persons with advanced cancer and their relatives. Self-management programs for this population with a format of video-conferencing group meetings are also new. A review showed that group interventions delivered by video-conferencing are acceptable and feasible in various populations (such as chronic disease, obesity, caregivers) [22]. In healthcare, telemedicine can be of considerable benefit to patients [57], and induced by the Covid-19 pandemic, it has taken off [58]. Therefore, examining this format for persons with advanced cancer and their relatives is a relevant next step.

Our SMART study has several risks. The study population and the program contain several factors that cannot be fully controlled. Firstly, there will be a considerable risk of drop out, either partly (some meetings) or completely, to disease progression or treatment burden of our vulnerable population [59]. To minimize this, we only include patients with a WHO performance status of 0 or 1 [60], and participants can choose when to start with the program to accommodate their schedule. Secondly, the risk of selection bias cannot be ruled out. Conducting research through self-referral, by online questionnaires and the video-conferencing group format, may primarily attract participants with higher digital literacy [61]. To minimize this risk, we offer technical support before and during the program, and explicitly explain that experience with video-conferencing applications is not necessary. Banbury and colleagues demonstrate that inexperience with video-conferencing or computer use was not a major problem for participation in video-conferencing groups [22]. Thirdly, while a randomized controlled trial (RCT) is preferred as a gold standard for measuring the effects of an intervention, we opt for a non-randomized stepped wedge design to make the study better feasible. Whilst we adjust for possible confounders in the analysis, residual confounding still remains a risk. Fourth, our program is a complex intervention, meaning it contains several interacting components, such as improving self-efficacy and behavior, the self-tailoring format, and group interaction [62]. Therefore, it may be difficult to identify the active components of the program. Combining the quantitative data of this study with the findings of our complementary qualitative study will provide insight into participants’ experiences and the perceived working mechanism of the program.

## Data Availability

The datasets used and/or analysed during the current study are available from the corresponding author on reasonable request.

## Abbreviations

CDSMP: Chronic Disease Self-Management Program
CD-RISC: Connor-Davidson Resilience Scale
CRA-D: Caregiver Reaction Assessment Dutch
GCQ-23: The Group Climate Questionnaire
HADS: Hospital Anxiety and Depression
HEIQ: Health Education Impact Questionnaire
ICC: intraclass correlation coefficient
MQOL: McGill Quality of Life
NRS: numeric rating scale
QOLLTI-F: Quality of Life in Life Threatening Illness Family Carer Version
RCT: Randomized Controlled Trial
SBSQ: Set of Brief Screening Questions
SCQ: Self-Administered Comorbidity Questionnaire
SES: Social Economic Status
SPIRIT: Protocol Items: Recommendations for Interventional Trials
UCLA: University of California, Los Angeles
WHO: World Health Organization
